#### Criteria for discontinuing or modifying allocated interventions

Titer of HBV DNA in blood will be determined every 12 weeks in all participants. If the titer of HBV DNA has not decreased significantly by 3 months after surgery, which suggests drug resistance, patients who have been receiving 300 mg/day of oral TDF will also be given 0.5 mg/day of oral entecavir, while patients who have been receiving 0.5 mg/day of oral entecavir will switch to only 300 mg/day of oral TDF. Otherwise, patients will continue on the same medication as at enrollment. All participants will receive antiviral therapy until death or the end of the study, given that there are no consensus guidelines on the length of antiviral treatment for patients with HBV-associated HCC. If serum HBV DNA has not decreased after one month of conversion therapy, patients will be switched to tenofovir alafenamide fumarate.

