**Methods:**

This study is a randomized, open-label trial. A total of 240 participants will be randomized 1:1 into groups receiving TDF or entecavir monotherapy. The two groups will be compared in terms of recurrence-free and overall survival at 1, 3, and 5 years after surgery; adverse events; virological response; rate of alanine transaminase normalization; and seroreactivity at 24 and 48 weeks after surgery.

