The primary outcome is recurrence-free survival, defined as the time between the randomization date and first occurrence of HCC recurrence, as detected by imaging. Recurrence can be extrahepatic or new intrahepatic. The secondary outcomes of this trial include overall survival, defined as the time between the randomization date and death. If the participant is alive at the end of the study or is lost to follow-up, the last follow-up visit will be used. Other secondary outcomes are virological response, defined as titer of HBV DNA; rate of alanine transaminase normalization; seroreactivity at 24 and 48 weeks after resection, defined as the presence of HBsAg or HBV e antigen; frequency of treatment-related adverse events, as assessed using the Common Terminology Criteria for Adverse Events (version 5.0) [32]; and treatment tolerability, measured in terms of the proportion of patients completing the planned treatment.

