#### Methods in analysis to handle protocol non-adherence and any statistical methods to handle missing data

Data analysis of this study will according to the intention-to-treat principle. Efforts are made to follow-up participants who dropped out from treatment in order to obtain more evaluation indexes and recorded in the CRFs. The last assessment data will be applied for patients who lost to follow-up.

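### Week-24 and week-48 virological, ALT and serological results compare starting-drug strategies that include unequal rescue, not the two monotherapies the protocol names

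*Protocol article*

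**What the plan says.** The section on discontinuing or modifying allocated interventions sets the trigger: "If the titer of HBV DNA has not decreased significantly by 3 months after surgery". When it is met, the two arms are handled differently. In the TDF arm, "patients who have been receiving 300 mg/day of oral TDF will also be given 0.5 mg/day of oral entecavir". In the entecavir arm, "patients who have been receiving 0.5 mg/day of oral entecavir will switch to only 300 mg/day of oral TDF". A second step applies to both arms: "If serum HBV DNA has not decreased after one month of conversion therapy, patients will be switched to tenofovir alafenamide fumarate".

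The Abstract (Methods) and Trial design list the secondary outcomes as "virological response; rate of alanine transaminase normalization; and seroreactivity at 24 and 48 weeks after surgery". The Outcomes section defines virological response as the HBV DNA titre and gives no time point for it. It ties the two weeks expressly only to "seroreactivity at 24 and 48 weeks after resection, defined as the presence of HBsAg or HBV e antigen". None of these definitions mentions conversion.

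The section on non-adherence and missing data states: "Data analysis of this study will according to the intention-to-treat principle". Objectives, Trial design and the explanation of the comparators all describe a comparison of two monotherapies. Objectives includes prevention of viral reactivation in the short term.

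**The concern.** Conversion comes before the read-outs, and its trigger is the variable that one of the outcomes measures. A patient who fails on entecavir and then clears virus on TDF, the comparator itself, stays in the entecavir arm and adds to its week-24 response rate. A patient who fails on TDF and clears virus on the combination adds to the TDF rate. Because the rescue differs by arm, the distortion need not cancel.

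What is at stake is the reading of the secondary efficacy results. The Background reports that earlier retrospective studies found no difference between the drugs in virological response. Similar week-24 rates here would naturally be taken as confirming that for the monotherapies, although rescue alone could produce them.

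**Working it through.** **The plan's own figure.** The only stated calculation is for recurrence-free survival, with 3-year rates of 64% and 79%, 90% power and two-sided 0.05. Under exponential survival the hazard ratio is ln(0.79)/ln(0.64) = 0.528, and Schoenfeld's formula gives 104 events. With two years of accrual and five further years of follow-up the mean event probability is 0.482, so 104/0.482/2 = 107.9 per arm, matching the stated 108. Then 216/0.9 = 240. This reproduces and does not depend on the point made here. No figure is stated for the week-24 and week-48 outcomes.

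**Order of events.**

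| Step | Time after surgery | Source |
|---|---|---|
| First conversion | month 3, about week 13 | modifying interventions |
| Second step | about a month later, about week 17 | same section |
| Read-outs | weeks 24 and 48 | Abstract, Trial design |

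Both read-outs follow both steps.

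**Effect with the same rescue success in both arms.** For each arm let N be the proportion who would be non-responders at the read-out on the allocated drug alone, t the share of them who are converted, and s the fraction of those converted who then respond. The document gives none of these, so all values below are assumed.

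- Observed non-response = N(1 − ts).
- With t and s equal in the two arms, observed difference = true difference × (1 − ts).

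For a true difference of 10 points:

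| | s = 50% | s = 90% |
|---|---|---|
| t = 25% | 10(1 − 0.125) = 8.75 | 10(1 − 0.225) = 7.75 |
| t = 100% | 10(1 − 0.5) = 5 | 10(1 − 0.9) = 1 |

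**Effect with unequal rescue success (t = 100%).**

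- Reversal: response on the allocated drug alone is 90% (TDF) and 80% (entecavir), with rescue success 70% and 90%. Observed response is 90 + 10 × 0.7 = 97% against 80 + 20 × 0.9 = 98%.
- Difference from nothing: 10% non-response in both arms, with rescue success 80% after add-on and 60% after switch. Observed non-response is 10 × 0.2 = 2% (TDF) against 10 × 0.4 = 4% (entecavir), although the monotherapies are equal.

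**Data available before conversion.** Table 1 schedules hepatitis B virology, including HBV DNA, and liver function (taken to include ALT) at one, two and three months. The month-3 values, taken before any conversion, are therefore already collected.

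**The case against.** **Intention to treat is legitimate, and the SAP may deal with conversion.** Both statements are fair. Comparing starting drugs together with their rescue rules is a valid question, and intention to treat does not forbid scoring conversion as non-response. If the only fault were a missing rule for conversion, it would be no finding. But the conversion rule, the read-out weeks, the analysis principle and the monotherapy objective are all stated in this document, and they do not fit together.

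**The read-out weeks are less firm than they look.** This stands in part. A reader might infer that all three outcomes are fixed at weeks 24 and 48. The Abstract and Trial design can be read that way, but the Outcomes section attaches the weeks only to seroreactivity. Any read-out after month 3 is affected in either case.

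**The loss could be overstated.** This stands. A reader might infer that the difference shrinks to (1 − s) of its true value. That requires every eventual non-responder to have been converted. The trigger is a titre that has not fallen significantly, so patients with a partial fall may never be converted. Nor should much be made of power at the extreme: for 1.5% against 0.5% non-response with 120 per arm, expected counts are 1.8 and 0.6. The normal approximation gives 12%, but exact power is 6% by chi-squared and 0.6% by Fisher's test.

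**Scoring conversion as failure brings its own bias.** This also stands. The protocol does not define a significant decrease, and investigators know the allocation. Some converted patients might have responded later on the allocated drug. For ALT and serology, a virological trigger would mark as failed a patient whose ALT is normal.

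**Conclusion.** The point holds as a mismatch between the stated question and what the secondary outcomes measure. As randomised, results after month 3 compare allocated drug followed by protocol rescue, with add-on in one arm and a switch to the comparator in the other. They do not compare the two monotherapies.

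The direction and size of the effect on virological response cannot be derived from the document. With equal conversion and rescue in the two arms, a 10-point difference becomes anything from 8.75 points (t = 25%, s = 50%) to 1 point (t = 100%, s = 90%). With unequal rescue it can reverse or arise from nothing. If few patients meet the trigger, the effect is small.

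Two stronger conclusions are tempting. One is that the week-24 and week-48 results are uninterpretable. They are not: they answer which starting drug, with the stated conversion rules, gives better viral control. The other is that the trial's size is undermined. The calculation for recurrence-free survival reproduces and is not affected by this point. This is a secondary-outcome matter that should be corrected, and cheaply.

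**What to change.** 1. Add a comparison of HBV DNA and ALT at the month-3 visit, before any conversion, as the direct monotherapy comparison. It uses data already scheduled in Table 1.
2. For virological response at weeks 24 and 48, add an analysis that counts conversion before the read-out as non-response, and report the number converted in each arm.
3. Keep the as-randomised week-24 and week-48 results, including ALT and serology. Label them as allocated drug followed by protocol rescue, and do not conclude from them that the monotherapies are similar or different.
4. Reconcile the wording of the conversion rule with the monotherapy objective. No change to patient care is proposed.

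The cost is outcome wording and two analyses of data already collected. Response rates in analysis 2 will be lower, and that analysis rests on an undefined trigger applied by unblinded investigators. The month-3 comparison should therefore carry the monotherapy conclusion, accepting that it speaks only to the first three months.

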#### Strategies to improve adherence to interventions

The intervention plans in this study belong to the clinical routine treatment, and both the incidence of serious adverse reactions and treatment costs are low. This study will adhere to the relevant regulations of medical ethics and Good Clinical Practice (GCP). Investigators will fully communicate with patients to improve compliance and minimize shedding and missing follow-up cases as much as possible.

#### Relevant concomitant care permitted or prohibited during the trial

Repeat hepatic resection, ablation, systemic chemotherapy, radiation therapy, targeted drugs, immunotherapy, and other anti-tumor treatments for recurrent HCC are permitted during the study [29–31]. At the investigators’ discretion, participants will also be allowed to continue long-term medications for chronic diseases such as hypertension or diabetes.

#### Provisions for post-trial care

The study will not provide specific provisions for post-trial care. Recommendations and referrals will be given by licensed clinical study staff to the participants who asked for additional clinical care.

### Outcomes

Patients will receive routine follow-up every month for the first three months, every two months for six months to two years, then every six months thereafter. At each follow-up, tests will be performed to assess liver function, HBV DNA load, virological response, serum alpha fetoprotein level, and other hematological indicators. Each follow-up will also involve liver ultrasonography as well as contrast-enhanced computer tomography of the chest and abdomen or magnetic resonance imaging of the abdomen (Table 1).

**Table 1 Tab1:** Study assessment measures

Assessment measures	Preoperation	Postoperative day 5	One month after surgery	Two months after surgery	Three months after surgery	Six months after surgery	Every six months until HCC recurrence /metastasis or death
Blood routine examination	x	x	x	x	x	x	x
Urine routines	x	x	x	x	x	x	x
Stool routine examination	x	x	x	x	x	x	x
Liver function	x	x	x	x	x	x	x
Renal function	x	x	x	x	x	x	x
Myocardial enzyme	x	x	x	x	x	x	x
Hepatitis B virological test^1^	x		x	x	x	x	x
Coagulation function	x	x	x	x	x	x	x
Lipid level^2^	x		x	x	x	x	x
Alpha fetoprotein	x		x	x	x	x	x
Des-gamma-carboxy prothrombin	x		x	x	x	x	x
Hepatits C antibody	x						
Human immunodeficiency virus antibody	x						
• Blood HCG test^3^	x						
Electrocardiogram	x		x	x	x	x	x
Abdominal ultrasonography	x		x	x	x	x	x
Chest and upper abdomen enhanced MRI/CT	x		x	x	x	x	x

*CT* Computed tomography, *HCC* Hepatocellular carcinoma, *MRI* Magnetic resonance imaging, *RFS* Recurrence-free survival, *OS* Overall survival

1. Including hepatits B surface antigen, hepatits B surface antibody, hepatits B e antigen, hepatits B e antibody, hepatits B c antibody, and hepatits B virus DNA

2. Including triglyceride, cholesterol, high-density lipoprotein, and low-density lipoprotein

3. Women of childbearing age

The primary outcome is recurrence-free survival, defined as the time between the randomization date and first occurrence of HCC recurrence, as detected by imaging. Recurrence can be extrahepatic or new intrahepatic. The secondary outcomes of this trial include overall survival, defined as the time between the randomization date and death. If the participant is alive at the end of the study or is lost to follow-up, the last follow-up visit will be used. Other secondary outcomes are virological response, defined as titer of HBV DNA; rate of alanine transaminase normalization; seroreactivity at 24 and 48 weeks after resection, defined as the presence of HBsAg or HBV e antigen; frequency of treatment-related adverse events, as assessed using the Common Terminology Criteria for Adverse Events (version 5.0) [32]; and treatment tolerability, measured in terms of the proportion of patients completing the planned treatment.

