### Trial design

This study is a phase 3 randomized, open-label, superiority trial. Participants will be randomly divided into two groups in a ratio of 1:1, one of which will receive TDF monotherapy and the other will receive entecavir monotherapy during the peri- and postoperative period. The primary outcome of the study is the rate of recurrence-free survival at 1, 3 and 5 years after curative hepatectomy. The secondary outcomes are the rate of overall survival at 1, 3, and 5 years; adverse reactions; virological response; rate of alanine transaminase normalization; and seroreactivity at 24 and 48 weeks after surgery.

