### Sample size

We estimated using PASS 15.0.5 that we would need at least 108 subjects in each group, assuming 3-year rates of recurrence-free survival of 64% among those on entecavir monotherapy [23] and anticipated 79% among those on TDF monotherapy, enrollment lasting two years and follow-up lasting five years. This sample should be able to detect a significant difference between the groups with 90% power and bilateral α = 0.05. We increased the total number from 216 to 240 to compensate for 10% loss to follow-up.

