### Statistical methods

#### Statistical methods for primary and secondary outcomes

All statistical analyses will be conducted in a blinded manner. Data will be reported as mean ± SD, and inter-group differences in continuous variables will be assessed for significance using Student's *t* test, while differences in categorical variables will be assessed using the chi-squared test. Survival curves will be calculated using the Kaplan–Meier method and compared using the log-rank test. Cox regression will be applied to identify factors associated with primary and secondary outcomes.

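### The primary outcome is called recurrence-free survival but counts only imaged recurrence as an event, so its planned rates are time-to-recurrence rates

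*Protocol article*

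**What the plan says.** Trial design in the protocol article sets the primary endpoint: "The primary outcome of the study is the rate of recurrence-free survival at 1, 3 and 5 years after curative hepatectomy". Outcomes then defines recurrence-free survival; it is "defined as the time between the randomization date and first occurrence of HCC recurrence, as detected by imaging". The next sentence says which findings qualify: "Recurrence can be extrahepatic or new intrahepatic". Death enters only with the secondary outcome, "overall survival, defined as the time between the randomization date and death". The sentence after that reads "If the participant is alive at the end of the study or is lost to follow-up, the last follow-up visit will be used". It follows the overall-survival definition and covers patients who are alive or lost, not patients who died without recurrence.

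The analysis is stated under Statistical methods for primary and secondary outcomes: "Survival curves will be calculated using the Kaplan–Meier method and compared using the log-rank test". Cox regression is added for associated factors. No competing-risk method is named. Sample size uses the survival label too, "assuming 3-year rates of recurrence-free survival of 64% among those on entecavir monotherapy", against 79% on TDF.

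**The concern.** Recurrence-free survival means being alive and without recurrence. The written event rule leaves out the first half. A patient who dies of liver failure, or of any other cause, before a scan shows recurrence never has a primary event. With Kaplan–Meier and log-rank methods and no other rule, that patient leaves the risk set at death and is treated as if recurrence could still have been seen later.

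The quantity estimated is then time to recurrence with deaths censored, reported under another name. The published 1-, 3- and 5-year figures would be too high as recurrence-free survival. The planning rates carry the same label, so it is also unclear which event the trial was sized for. This is the primary endpoint of a phase 3 superiority trial, and the mismatch lies in a complete, stated definition. It is not a detail left to another document.

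**Working it through.** **1. The plan's own figure.** Inputs from Sample size: 3-year rates 64% and 79%, two years of enrolment, five years of follow-up, 90% power, two-sided α = 0.05, 10% loss. I assume exponential times.

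- Yearly hazards: −ln(0.64)/3 = 0.1488 (entecavir) and −ln(0.79)/3 = 0.0786 (TDF). HR = 0.0786/0.1488 = 0.528.
- Events (Schoenfeld): 4 × (1.960 + 1.282)² / (ln 0.528)² = 103.2, so 104.
- Mean event probability with uniform accrual over 2 years plus 5 further years: (0.589 + 0.375)/2 = 0.482.
- Patients: 104/0.482 = 215.7, so 108 per arm. 216/0.90 = 240. Power at 216 is 0.903.

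The stated 108 and 240 reproduce. The point concerns the definition, not this arithmetic.

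**2. Assumption on deaths.** The protocol gives no rate of death without recurrence. I take a net 5-year death probability m (the probability if recurrence did not occur) of 5% to 10%, equal in both arms, and first treat 64%/79% as recurrence-only rates. The death hazard is d = −ln(1 − m)/5, which is 0.0103 per year (m = 5%) or 0.0211 (m = 10%).

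**3. Effect on the 5-year rates.** With recurrence hazard λ, the written definition estimates exp(−5λ), while recurrence-free survival is exp(−5(λ + d)).

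| | Entecavir | TDF | Difference |
|---|---|---|---|
| As written | 47.5% | 67.5% | 20.0 points |
| Deaths counted, m = 5% | 45.2% | 64.1% | 19.0 points |
| Deaths counted, m = 10% | 42.8% | 60.8% | 18.0 points |

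**4. Patients affected.** The probability of dying first is d/(λ + d) × P(any event), averaged over 5 to 7 years of follow-up.

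- m = 5%: 0.0396 (entecavir) and 0.0476 (TDF), so 120 × (0.0396 + 0.0476) = 10.5 patients.
- m = 10%: 0.0791 and 0.0950, so 120 × (0.0791 + 0.0950) = 20.9 patients.

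The shares who actually die first by 5 years are lower than m, because recurrence often comes first: 3.5% and 4.1% for m = 5%, 7.1% and 8.3% for m = 10%.

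**5. Power if deaths become events.** The composite HR is (0.0786 + d)/(0.1488 + d), and power is Φ(½√D × |ln HR| − 1.96) with D events among 216 patients.

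- m = 5%: HR 0.559, D = 110.8, power 0.87.
- m = 10%: HR 0.587, D = 117.3, power 0.82.
- Wider range: at a death hazard of 5% per year, HR 0.647 and power 0.71.

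**6. If 64%/79% already count death.** Then 108 per arm stands for the composite endpoint, but the written definition would still report higher figures. With a death hazard of 1% per year inside those rates, the 3-year figures become 65.9%/81.4%; with 2%, 68.0%/83.9%.

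**The case against.** The protocol never says that deaths are censored. Table 1 runs the six-monthly assessments up to recurrence, metastasis or death, and with the word survival in the name this could suggest a composite that was loosely drafted. Detailed censoring rules often sit in an analysis plan or a full protocol, and neither is shown. It stands that censoring at death is a consequence of the stated event rule and method, not a stated rule. But a visit schedule does not make death an event, and an analysis plan that added death would contradict the definition in Outcomes.

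The effect is also modest. In the assumed range the 5-year difference moves by 1 to 2 points, and the recurrence-only comparison at 216 patients keeps power of about 0.89. Deaths are still compared between arms through overall survival. All of this limits the size of the problem, but it does not make the primary rates what their name says.

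A reader might go further. Background and rationale credits the drugs with lowering the risk of liver failure, so one could infer that these deaths lie on the treatment pathway, that censoring is informative, and that the comparison is biased. The document does not support this. It makes that statement about both drugs and claims no difference between them. Informative censoring would need death and recurrence risk to be linked within an arm, which is plausible but not stated there.

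**Conclusion.** The mismatch between name and event definition is certain from the text and should be settled before outcome data are analysed. Followed as written, with the planned methods, the protocol would report time-to-recurrence rates as recurrence-free survival, and they would be too high. The overstatement at 5 years is about 2.4 and 3.4 points (entecavir, TDF) at a net death probability of 5%, and about 4.8 and 6.8 points at 10%.

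These sizes rest on four assumptions: constant hazards, equal death hazards in both arms, the 5% to 10% range, and planning rates that count recurrence only. The last cannot be checked here, because 64% comes from a cited study. The direction of the error does not depend on it. Bias between the arms is possible if death rates differ, but the documents do not show it.

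**What to change.** In Outcomes, choose one of two definitions:

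- **Keep the name.** Time from randomisation to the first of imaging-detected recurrence (intrahepatic or extrahepatic) or death from any cause, with all others censored at the last recurrence-free assessment. Report time to recurrence as supportive, using cumulative incidence with death as a competing event.
- **Keep the event.** Rename the primary outcome time to recurrence throughout, and analyse death as a competing event. This also fits the stated objective of preventing recurrence.

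Then confirm in Sample size that 64% and 79% use the chosen definition. If death is to be an event and those rates already count it, 108 per arm stands. If they are recurrence-only, restate the power at 216 evaluable patients (about 0.87 to 0.82 in the assumed range). Enlarging the trial is not a realistic answer: the Discussion reports that the ethics committee did not approve an increase to 638.

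The cost is a short protocol amendment, with the registry updated alongside as the protocol already provides. Under the first option the stated rates are slightly lower and the stated power may be lower. No new data are needed, because deaths are already collected for overall survival.

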## Abstract

**Background:**

Entecavir and tenofovir disoproxil fumarate (TDF) are standard first-line treatments to prevent viral reactivation and hepatocellular carcinoma (HCC) in individuals chronically infected with the hepatitis B virus (HBV), but the long-term efficacy of the two drugs remains controversial. Also unclear is whether the drugs are effective at preventing viral reactivation or HCC recurrence after hepatectomy to treat HBV-associated HCC. This trial will compare recurrence-free survival, overall survival, viral indicators and adverse events in the long term between patients with HBV-associated HCC who receive entecavir or TDF after curative resection.

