#### Adverse event reporting and harms

Adverse events will be assessed using the Common Terminology Criteria for Adverse Events (version 5.0) [32]. Adverse events and serious adverse events (SAE) will be recorded including name of adverse event, start time, end time, degree, correlation with study drug, and accompanying treatments. In addition to complying with the requirements of the SAE report of the department, it is also necessary to report to the ethics committee of the principal investigator within 24 h of being informed of the occurrence of SAE. Follow up will carry on until the event is resolved or the condition of the participant return to baseline.

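### Table 1 ends scheduled safety tests at HCC recurrence while the study drug continues, so a crude adverse-event frequency may depend on the primary endpoint; the post-recurrence rules must be reconciled

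*Protocol article*

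**What the plan says.** - **Aim.** The Abstract (Background) says the trial will compare "viral indicators and adverse events in the long term".
- **Outcome.** The Outcomes section lists as a secondary outcome the "frequency of treatment-related adverse events, as assessed using the Common Terminology Criteria for Adverse Events (version 5.0". It gives no time window and no denominator, although seroreactivity in the same sentence has fixed time points (24 and 48 weeks).
- **Test schedule.** The last column of Table 1 is headed "Every six months until HCC recurrence /metastasis or death". It covers the repeated blood, urine, liver, renal, cardiac-enzyme, coagulation, lipid and ECG assessments. Plans for assessment and collection of outcomes refers to Table 1 for timing.
- **Visit prose.** The text above Table 1 ends the visit schedule with "then every six months thereafter" and names no stop at recurrence.
- **Drug duration.** Criteria for discontinuing or modifying allocated interventions states: "All participants will receive antiviral therapy until death or the end of the study". The same section says: "Titer of HBV DNA in blood will be determined every 12 weeks in all participants".
- **Recording rule.** Adverse event reporting and harms states: "Adverse events and serious adverse events (SAE) will be recorded including name of adverse event, start time, end time, degree, correlation with study drug". It sets no cut-off at recurrence.
- **Analysis.** Statistical methods says in general terms that "differences in categorical variables will be assessed using the chi-squared test". Adverse events are not named there.

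**The concern.** In a patient whose tumour recurs, Table 1 stops the scheduled safety tests while the drug goes on. Renal, hepatic and lipid toxicity is found largely by testing, so the time during which it can be found is cut short by the primary endpoint event. The trial is powered on the expectation that this event differs between arms. A frequency that ignores observation time then compares arms observed for different lengths of time, to the disadvantage of the arm with fewer recurrences. An analysis plan could adjust for the difference in length, but it could not recover laboratory events that were never measured after recurrence.

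**Working it through.** **Inputs.** From Sample size: 3-year recurrence-free survival 64% (entecavir) and 79% (TDF), two years of enrolment, five years of follow-up, 90% power, two-sided 0.05. The documents give no adverse-event rate, so the rate *a* below is an assumption, equal in both arms. Other assumptions: exponential recurrence, deaths ignored.

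**1. Hazards, and the plan's own figure.**
- λ = −ln(S)/3 gives 0.1488 per year (entecavir) and 0.0786 per year (TDF). The hazard ratio is ln 0.79 / ln 0.64 = 0.528.
- Schoenfeld's formula, 4(1.960 + 1.282)² / (ln 0.528)², gives 104 events after rounding up.
- With uniform accrual over 2 years and 5 further years (7 in total), the mean event probability is 0.482. Then 104 / 0.482 / 2 = 107.9, or 108 per group, and 216 / 0.90 = 240. The stated sample size is reproduced, so these hazards are a fair reading of the protocol's assumption.

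**2. Scheduled-test time if Table 1 governs.** Mean time to recurrence within horizon H is (1 − e^(−λH))/λ.

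| Horizon | Entecavir | TDF | Ratio |
|---|---|---|---|
| 3 years | 2.42 y | 2.67 y | 1.10 |
| 5 years | 3.53 y | 4.13 y | 1.17 |
| 5–7 years, averaged over accrual | 3.96 y | 4.78 y | 1.21 |

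At 5 years, 1 − 3.53/5 = 29% (entecavir) and 1 − 4.13/5 = 17% (TDF) of planned treatment time has no scheduled safety test.

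**3. Effect on a crude proportion.** Suppose events are found only by scheduled tests. The proportion with an event before recurrence by 5 years is a/(a+λ) × (1 − e^(−5(a+λ))).

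| Assumed rate *a* per year | Entecavir | TDF | Difference | Ratio |
|---|---|---|---|---|
| 0.02 | 6.8% | 7.9% | 1.1 points | 1.17 |
| 0.05 | 15.8% | 18.4% | 2.6 points | 1.16 |
| 0.10 | 28.6% | 33.1% | 4.5 points | 1.16 |

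With 120 per arm these differences are about 1, 3 and 5 patients. The chance of a falsely significant excess on TDF is about 5%, 8% and 11%, against a nominal 2.5%. At a much higher assumed rate of 0.40 per year, the proportions are 68.2% and 75.9%.

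**4. Conditions under which it fades.**
- Events arising only in the first year at 0.10 per year: 8.9% versus 9.2%, ratio about 1.03.
- Equal recurrence in the two arms: equal λ, so no difference.

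**5. Which analyses remove it.**
- *First events per patient-year.* Mean time at risk is (1 − e^(−5(a+λ)))/(a+λ). Dividing the proportion in step 3 by this gives *a* in both arms. At a = 0.05, 0.158/3.17 and 0.184/3.69 are both 0.05.
- *Cumulative incidence with recurrence as a competing event.* Under these assumptions this is the formula in step 3, so it returns 15.8% versus 18.4% and leaves the problem in place.

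**The case against.** A reader might infer that TDF will look more toxic than it is. The documents do not support that.

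- **Ending scheduled tests is not ending adverse-event capture.** The adverse-event section has no cut-off at recurrence, the visit prose has none, HBV DNA is measured in all participants every 12 weeks, and overall survival is followed to 5 years. Symptomatic and serious events may well be counted after recurrence. This stands, and it is why the point is conditional on Table 1 governing. It does not dispose of the point: laboratory toxicity needs the tests that Table 1 ends, and HBV DNA is not a safety test.
- **The direction is not fixed.** Relevant concomitant care permits several anti-tumour treatments for recurrent HCC. If events are captured after recurrence, the arm with more recurrences could record more of them, some perhaps attributed to the study drug. This also stands.
- **Analysis detail may sit elsewhere.** A reader might also infer that the protocol commits to a chi-squared test of adverse events. The sentence on categorical variables is general, frequency is not defined as a per-patient proportion, and an exposure-adjusted method may be in an analysis plan that is not shown. Its absence here is therefore not the finding. The finding is the mismatch between the Table 1 stop, the visit prose, the recording rule and the treatment duration, all of which are protocol matters.
- **The size is modest.** It rests on assumed event rates and on events being found only by scheduled tests. Agreed.

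**Conclusion.** The point holds in conditional form. The protocol contradicts itself on what happens after recurrence: Table 1 stops safety tests, the visit prose and adverse-event section state no stop, and treatment continues. If Table 1 is followed, laboratory safety observation depends on the primary endpoint. It would be about 17% longer on TDF over 5 years under the protocol's own survival assumptions (exponential, deaths ignored). A crude frequency may then overstate toxicity in the arm with fewer recurrences, by about 1 to 4.5 percentage points at assumed equal true rates of 2% to 10% per year.

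That size needs a real difference in recurrence, similar true event rates, and late events detected mainly by scheduled tests. It concerns a secondary outcome. It should be corrected because the change is cheap and the dependence on arm follows from the schedule as written.

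**What to change.** 1. **Reconcile the passages.** Table 1, the visit prose in Outcomes, the treatment-duration statement and the adverse-event section should agree on what happens after recurrence. Outcomes and Adverse event reporting and harms should state whether adverse events are recorded after recurrence, with the same rule in both arms.
2. **Define the measure in Outcomes.** Report treatment-related adverse events by randomised arm as events per patient-year of safety observation, or as time to first event censored at the end of safety observation. Using the randomised arm matters because the protocol lets patients switch or add the other drug.
3. **Add a common early window.** Also report the proportion with an event in a window common to all patients, for example to week 48. Recurrences within that window would leave only a small residual imbalance (ratio about 1.03 in the first-year calculation).
4. **Do not use cumulative incidence with recurrence as a competing event for this purpose.** It reproduces the bias.

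Cost: wording and a minor extra analysis. Event start and end times are already to be recorded. The end date of safety observation is not among the items the adverse-event section lists, so it must be captured for each patient. The rate assumes a roughly constant event rate, and the censored analysis assumes that recurrence carries no information about toxicity. The early window is a useful check on both.
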